### Participants

All NYS Office of Mental Health (OMH) child-serving public outpatient mental health clinics across the five boroughs of New York City (NYC) are eligible to participate. To secure the sample of clinics, the study team obtained a master list of 168 clinics from OMH. Based on prior statewide studies conducted by the investigative team, it was estimated that approximately 80% of the clinics would participate; thus, we estimated that approximately 134 clinics will enroll in the study.

At each clinic, we anticipate enrolling 20 caregiver/child dyads (a minimum of *n* = 896 per arm, or 2688 total), and two providers per arm, yielding a total of 268 providers. Researchers will consecutively consent families to participate in the study until a sample of 20 caregiver/child dyads per clinic is achieved. Eligible caregivers are 18 years of age or older, English or Spanish speaking, and the primary caregiver of a 7- to 11-year-old child with ODD. Eligible providers are staff members who work in a participating clinic in a clinical capacity, and are English speaking.

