### Sampling procedure

A multi-stage sampling procedure was undertaken, with randomization occurring at the agency level in order to prevent an unbalanced representation of clinics across the treatment arms and to conduct a sub-study in which we will examine the impact of clinic choice upon outcomes. From a master list of OMH-licensed agencies and corresponding clinics within the five boroughs of NYC that was received from The Office of Mental Health in 2016, the investigative team created three lists: (1) single-site (agencies that had only one outpatient mental health clinic, (2) multi-site agencies with between two to four clinics and, (3) mega-agencies that had five or more clinics. Each list was organized alphabetically.

A separate randomization process was employed for each list. Clinics within single-site agencies were stratified by borough, and a random number generator was employed to randomly assign clinics to one of three conditions: (1) condition 0, which was services as usual (SAU), (2) condition 1, the 4Rs and 2Ss MFG, and (3) condition 2, the 4Rs and 2Ss MFG + CIT (all three conditions are described more thoroughly on page 8). Once the initial number was generated, subsequent clinics were assigned the next number in the sequence (e.g., if the first clinic received condition 0, the next clinic would be enrolled in condition 1, and so forth). Of note, the research staff member was unaware what numbers corresponded with which condition (e.g., that a clinic in condition 0 would be randomized to SAU). This procedure was undertaken in order to minimize allocation bias.

Multi-site agencies with between two and four clinics were also organized alphabetically within borough, and a random number generator was used to assign the initial clinic to a particular condition. Moreover, additional clinics that were part of the agency in which the initial clinic was randomized received the same condition. For example, if one clinic was assigned condition 0, the remaining clinics, regardless of which borough they were located in, were also assigned to condition 0.

Finally, agencies with five or more clinics were given the choice to select the study condition in which they would participate with an even distribution of these mega agencies occurring across the three study conditions.

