### Description of the conditions

The study consists of three arms: two active treatment and one comparison condition:The 4Rs and 2Ss Multiple Family Group interventionThe 4Rs and 2Ss MFG is a 16-week group for urban children of between 7 and 11 years of age with ODD and their caregiver(s). In this model, six to eight families meet in weekly sessions focused on addressing family and parenting factors associated with behavior problems [30–33]. Session content also addresses lack of social support and high stress, which are two factors known to hinder treatment attendance [34–36]. Families are provided with free childcare, transportation expenses, and a meal to address common logistical barriers to attendance [8]. Moreover, perceptual barriers, such as stigma and fears of being blamed for their child’s difficulties, are targeted through group processes which normalize family difficulties, validate their expertise in solving problems, and promote mutual aid [37]. Providers who participate in this condition will attend a 5-h training to learn the 4Rs and 2Ss MFG model; thereafter, they will participate in bimonthly supervision over the course of implementationThe 4Rs and 2Ss MFG + CITIn addition to implementing the model and receiving supervision, a CIT consisting of providers, a clinic director and supervisor will participate in ongoing meetings with the research team’s adaptation specialist for a guided analysis of the structure, content and processes of the treatment model, including those that are amenable to modification and those that must remain unchanged in order to maintain fidelityStandard careStandard care includes the services that the clinic normally provides to children with behavioral problems, including outpatient mental health therapy and pharmacology

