### Hypotheses and data analytic strategy

The purpose of this study is to examine outcomes associated with the 4Rs and 2Ss MFG, implementation processes that impact uptake and sustained use of the intervention over time, and the impact of an innovative change agent team upon outcomes. The following hypotheses will be tested:
*Aim #1*: to examine the short-term and longitudinal impact of 4Rs and 2Ss MFG on child ODD and functioning
*Hypothesis #1*: youth who participate in 4Rs and 2Ss MFG will display significantly reduced conduct difficulties and increased functioning over time compared to those involved in standard care: youth in the 4Rs and 2Ss MFG + CIT condition will evidence the greatest magnitude of change in outcomes over time
*Aim #2*: to examine family level mediators (e.g., parenting, family process) of child outcomes
*Hypothesis #1*: based on existing 4Rs and 2Ss MFG findings, specific family level variables (caregiver stress, the parent/child relationship and established rules) will be associated with significantly greater impact on child outcomes over time relative to social support, established responsibilities, and respectful communication
*Aim #3*: to examine clinic- (readiness to adopt an innovation, leadership support, and climate) and provider-level moderators (engagement, preparedness, motivation) of 4Rs and 2Ss MFG implementation and integration
*Hypothesis #1*: leadership support will evidence significantly greater impact on 4Rs and 2Ss MFG implementation/integration in comparison to general readiness and clinic climate
*Hypothesis #2*: provider motivation will evidence significantly greater impact on 4Rs and 2Ss MFG implementation/integration relative to other provider-level variables
*Aim #4*: to examine the impact of CITs on clinic- and provider-level moderators of 4Rs and 2Ss MFG implementation and integration
*Hypothesis #1*: clinic directors assigned to MFG + CIT will evidence significantly higher readiness for innovation and support, and providers assigned to MFG + CIT will evidence significantly higher preparedness and motivation to implement MFG relative to MFG alone
*Hypothesis #2*: preparedness, motivation of providers, and leadership support assigned to MFG + CIT will be maintained over time and be significantly higher relative to MFG alone
*Hypothesis #3*: providers assigned to MFG + CIT will evidence significantly enhanced fidelity to MFG relative to MFG only

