### Trial status

Clinic recruitment for standard care has been completed. Data collection has been initiated, and one third (*n* = 792) of the sample of providers and caregivers have been enrolled. Clinic recruitment for MFG and MFG + CIT have been initiated, and some clinics have already completed training and have participated in adaptation meetings. Recruitment of clinics for the experimental arms will be ongoing until enrollment targets are met. Groups for both MFG and MFG + CIT are expected to begin in the first trimester of 2017. A populated Standard Protocol Items: Recommendations for Interventional Trials (SPIRIT) Checklist (see Additional file 1) and Figure ( see Fig. 3) for all study protocols are included as an additional file (see Additional file 1 and Fig. 3). A composition of the data monitoring commitee has also been included (see Additional file 2).

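### Aim 4 compares providers who enter after their clinic's condition is fixed, so the MFG + CIT versus MFG contrasts in preparedness, motivation and fidelity are open to post-assignment selection

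*Protocol article*

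**What the plan says.** **Assignment.** The Sampling procedure section states: "A multi-stage sampling procedure was undertaken, with randomization occurring at the agency level". For single-site agencies, "a random number generator was employed to randomly assign clinics to one of three conditions". In agencies with two to four clinics, "additional clinics that were part of the agency in which the initial clinic was randomized received the same condition". Mega-agencies were not randomised: "agencies with five or more clinics were given the choice to select the study condition in which they would participate". The frame was a list of agencies and clinics; no list of providers is mentioned.

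**Provider entry.** The Participants section says: "Eligible providers are staff members who work in a participating clinic in a clinical capacity, and are English speaking". It expects 268 providers in total. Families are consented consecutively up to 20 dyads per clinic, but no comparable rule is given for providers. The Ethical issues section makes provider participation voluntary.

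**What each arm asks.** Under Description of the conditions, MFG providers attend a 5-hour training and then bimonthly supervision. MFG + CIT adds that "a CIT consisting of providers, a clinic director and supervisor will participate in ongoing meetings" with the adaptation specialist.

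**Timing.** Trial status reports that clinic recruitment for standard care is complete. It adds: "Recruitment of clinics for the experimental arms will be ongoing until enrollment targets are met". Some clinics had already been trained and had taken part in adaptation meetings.

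**Hypotheses and analysis.** Aim 4, Hypothesis 1 expects that "providers assigned to MFG + CIT will evidence significantly higher preparedness and motivation to implement MFG relative to MFG alone". Hypothesis 2 expects preparedness, motivation and leadership support to stay higher under MFG + CIT. Hypothesis 3 expects better fidelity there. The Abstract plans provider measurement at baseline. The Analytic strategy names baseline covariates at the family level and none in the provider-level model for Aims 3 and 4.

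**The concern.** When a cluster's condition is known before its individual participants are enrolled, those who enter can differ between arms even if the clusters were properly randomised. Here the two arms share one eligibility text but not one workload. MFG + CIT adds a seat on a change team and continuing meetings, so a clinic or provider who knows the condition has a documented reason to decide differently about who takes part.

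Preparedness, motivation and fidelity are traits on which willing members of a change team could already differ from other staff. A difference brought in by selection would look the same as a CIT effect. Motivation and preparedness can at least be measured before the CIT begins. Fidelity to MFG has no value before MFG is delivered, so Hypothesis 3 has no baseline of its own outcome to adjust for.

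At stake are the provider contrasts of Aim 4 and the provider link in the causal chain set out under Purpose of this study, which runs from CIT through clinic and provider to family and child.

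**Working it through.** **1. Providers per clinic.** 168 clinics × 0.80 = 134.4, stated as about 134. 134 × 2 = 268, which reproduces the stated provider total. The total therefore means two providers per clinic, although the Participants section prints two per arm.

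**2. Order of events.** Conditions were set from a list of agencies and clinics. A provider qualifies by working in a clinic that already participates. Clinics for the active arms are being recruited by named arm. Together these imply that providers enter after the condition is set. The article does not say so outright.

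**3. Possible size.** The article gives no staff numbers, provider SD, intraclass correlation (ICC) or share of clinics that would select. All of the following are assumptions:
- clinics per arm k = 134/3 = 44.7, with two providers each
- m eligible staff per clinic, m = 3 to 8
- a share q of CIT clinics enters its keenest two, and the other clinics enter two at random
- keenness correlates r with the outcome
- no true CIT effect; two-sided 5% test; ICC 0 to 0.2; clustering by agency ignored

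Spurious difference in SD units: d = (q in CIT − q in MFG) × r × T, where T is the mean of the top two of m standard normal values. By simulation, T = 0.423 (m = 3), 0.665 (m = 4), 0.956 (m = 6) and 1.138 (m = 8).

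Standard error: SE = √[2(1 + ICC)/(2k)] = √[(1 + ICC)/44.7], which is 0.150 at ICC 0 and 0.164 at ICC 0.2.

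False-positive rate = Φ(d/SE − 1.96) + Φ(−d/SE − 1.96).

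Worked case, m = 4, r = 0.5, q = 0.5 in CIT and 0 in MFG: d = 0.5 × 0.5 × 0.665 = 0.166.
- ICC 0: d/SE = 1.11, rate = Φ(−0.85) + Φ(−3.07) = 0.199
- ICC 0.2: d/SE = 1.01, rate = Φ(−0.95) + Φ(−2.97) = 0.174

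False-positive rates at r = 0.5 with no selection in MFG clinics (range over ICC 0 to 0.2):

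| m | q = 0.25 | q = 0.5 | q = 1 |
|---|---|---|---|
| 3 | 6.2–6.4% | 9.9–10.9% | 25–29% |
| 4 | 8.0–8.6% | 17–20% | 53–60% |
| 6 | 11–13% | 31–36% | 83–89% |
| 8 | 14–16% | 41–48% | 94–97% |

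The lowest cell calculated (m = 3, r = 0.3, q = 0.1) gives d = 0.013 and 5.1%. If both arms select alike, d = 0 and the rate is 5%. If MFG clinics select more than CIT clinics, d is negative and a true CIT effect is masked. With r at 0.5 or below, no cell calculated exceeds 50% unless every CIT clinic and no MFG clinic selects.

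**4. Room to act when the article was written.** Clinic involvement reports data collection at 8 MFG and 7 MFG + CIT clinics. An even split of 134 gives about 89 active-arm clinics, so about 89 − 15 = 74 had not started. How many of those are mega-agency or sister clinics is not stated.

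**The case against.** The strongest reply is that the article is only silent. It gives provider eligibility and number. How the two are identified may stand in the full protocol, and covariate detail may stand in the analysis plan. Nomination before disclosure would fit the text. This stands in part: a missing selection rule is no error in itself, and the point rests on the order of entry and the unequal workload, both drawn from the article.

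A reader might take the word *assigned* in Aim 4 as a mistake because providers are not randomised. It is ordinary cluster-trial usage for providers who take their clinic's condition.

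A reader might also infer that CIT clinics enter their keener staff, so that the bias favours MFG + CIT. The documents do not support that. MFG alone also asks for training, a 16-week group, supervision and fidelity checks, so willing staff may come forward in both arms. Extra meetings could equally lead a clinic to send whoever has time.

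Three further limits stand. Baseline provider data allow a motivation imbalance to be seen and partly adjusted for, if they are taken before the CIT meetings. Extra support for providers below 80% fidelity may narrow differences in Hypothesis 3. And child behaviour and functioning are the primary outcomes; Aim 4 concerns mediators.

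**Conclusion.** The point holds as an open route to bias, not as a demonstrated one. That providers enter after assignment is a sound inference, and the added CIT duties are a documented reason why entry could differ between the two MFG arms. The exposure is confined to the provider parts of Aim 4, Hypotheses 1 to 3, and is hardest to repair for fidelity. Directors' readiness and leadership support do not depend on which two staff are entered.

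Occurrence, direction and size cannot be established from the article. Every rate above rests on assumed staff numbers, correlation and ICC and, decisively, on how far selection differs between the arms. The large figures are a worst case, should not be quoted as the expected error rate, and describe an unadjusted contrast such as motivation. No estimate for fidelity is possible from what is given. An inexpensive safeguard is worth adopting; the primary comparison of the trial is not called into question.

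**What to change.** 1. **Randomised single-site clinics and multi-site agencies not yet told their condition.** Both active arms deliver MFG, so have each clinic name the two providers who will run it, and collect their baseline measures, before disclosing MFG or MFG + CIT. Analyse those named providers in their clinic's condition.
2. **Analysis.** Adjust the Aim 4 motivation and preparedness contrasts for the provider baseline where it precedes any CIT meeting. Fidelity cannot be handled this way and depends on step 1.
3. **Where concealment is impossible.** This covers mega-agencies that chose their condition, sister clinics of an agency that knows its condition, and clinics already started. Report Aim 4 with and without them, and describe their provider contrasts as open to selection.
4. **Wording.** State how the two providers per clinic are identified. If a rule already exists in the full protocol, a sentence is enough. Correct the provider count to per clinic.

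The cost is a change in the order of clinic onboarding and a short amendment. The downside is that clinics agree before knowing whether CIT meetings apply to them, and some named providers may later decline those meetings yet stay in the analysis. If clinic recruitment has closed, only steps 2 to 4 remain available.

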### Analytic strategy

The overall analytic structure uses a three-level, multi-level Structural Equation Modeling (MSEM) framework with family level variables at level 1, provider variables at level 2, and clinic variables at level 3. The analytic structure is complex, so we highlight our approach using Fig. 2 as our primary reference. The MSEM framework is useful because it ultimately allows a test of these aims within an integrated path modeling structure.

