**Fig. 2 Fig2:**
[figure not shown]
Analysis of mechanisms

We will employ mediation analysis with two-level MSEM models as explicated by Preacher, Zhang and Zyphur [57] and extended to three-level models by Preacher [57]. We will use a combination of limited information estimation frameworks (focused on sub-portions of the full model) and full information estimation frameworks (focused on the entire three-level model) to strategically answer questions. At level 1, child outcomes at the immediate post test are modeled as a function of the family predictors (see Fig. 2) using baseline measures of outcomes and family mediators as covariates, taking into account the clustering at the higher levels of the model. The follow-up (6-month) measures of the mediators and the outcomes are included within the model in a classic SEM panel model with autoregressive effects, thereby linking the follow-up data to the immediate post-test data. This is an advantage of using MSEM over traditional multi-level modeling. Different centering strategies (e.g., grand mean versus group mean) can be explored to garner various perspectives on the data. This feature of the model provides perspectives on aim 2 and the relative importance of paths g–l in Fig. 1. To ascertain perspectives of the effects of clinic-level variables on provider variables, random intercept MSEM with the provider-level variables can be estimated as a function of the clinic variables that include dummy coded treatment variables (4Rs and 2Ss MFG + CIT versus 4Rs and 2Ss MFG) impacting the clinic mediators of readiness, leadership support, and climate, which in turn, affect the provider-level intercepts. This modeling, or variants of it, address aims 3 and 4.

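### Agencies of two to four clinics are allocated as a block, but the model's top level is the clinic, so the standard errors of the arm contrasts may be too small

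*Protocol article*

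**What the plan says.** Under Sampling procedure the protocol article states: "A multi-stage sampling procedure was undertaken, with randomization occurring at the agency level". It sorts agencies into three lists.

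- Single-site: "agencies that had only one outpatient mental health clinic". Clinic and agency are the same unit.
- Multi-site: "multi-site agencies with between two to four clinics". One draw is made for the first clinic, and then "additional clinics that were part of the agency in which the initial clinic was randomized received the same condition". Borough does not split an agency. In the article's example, "the remaining clinics, regardless of which borough they were located in, were also assigned to condition 0".
- Mega: "agencies with five or more clinics were given the choice to select the study condition in which they would participate". These were not randomised.

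Under Analytic strategy the structure is a three-level structural equation model with "family level variables at level 1, provider variables at level 2, and clinic variables at level 3". The child-outcome model is fitted "taking into account the clustering at the higher levels of the model", and those higher levels are provider and clinic. For Aims 3 and 4, treatment enters as dummy variables among the clinic variables. The alternative growth-curve model also relates growth to provider and clinic variables only. The article mentions no agency effect, agency level or agency-clustered standard error.

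**The concern.** For multi-site agencies, the unit that received an allocation is larger than the largest unit in the model. Clinics of one agency are always in the same arm, so anything they share (management, policy, case mix) does not cancel between arms. It adds directly to the variance of the arm contrast. A model whose top level is the clinic absorbs agency variance into clinic variance and then counts each clinic as an independent replicate. With positive correlation between clinics of an agency, the standard error is too small, the degrees of freedom are too many and the test rejects too often.

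The contrasts at stake are those of Aim 1, which carries the primary outcomes (child behaviour and functioning), and Aim 4, which compares MFG + CIT with MFG alone.

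**Working it through.** **The article's own figures (Participants).** 168 clinics × 0.80 = 134.4 clinics. 134.4 × 20 dyads = 2688 dyads. 2688 / 3 = 896 per arm. 134 × 2 = 268 providers. All reproduce. The article states no power, alpha, effect size or ICC, so there is no power figure to check.

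**Inputs.**
- From the article: 20 dyads per clinic; k = 2 to 4 clinics per multi-site agency, k = 1 for single-site.
- Assumed, because the article gives none: total ICC above the family 0.05, of which 0.01 or 0.025 lies between agencies and the rest between clinics. These are read as residual values after baseline adjustment. Provider-level variance is not modelled separately.

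**Formulas.**
- Correlation between the means of two clinics of one agency: rho = ICC_agency / [ICC_agency + ICC_clinic + (1 − ICC_agency − ICC_clinic)/20].
- Variance understatement: VIF = 1 + (k − 1) × rho. The true standard error is √VIF times the one the clinic-level model reports.
- Actual two-sided error of a nominal 5% test: 2 × [1 − Φ(1.96/√VIF)].

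**rho.** The denominator is 0.05 + 0.95/20 = 0.0975. For agency ICC 0.01, rho = 0.01/0.0975 = 0.103. For agency ICC 0.025, rho = 0.025/0.0975 = 0.256.

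**All clinics in agencies of size k.**

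| k | Agency ICC | VIF | √VIF | Actual type I error |
|---|---|---|---|---|
| 1 | any | 1.00 | 1.00 | 5.0% |
| any | 0 | 1.00 | 1.00 | 5.0% |
| 2 | 0.01 | 1.10 | 1.05 | 6.2% |
| 2 | 0.025 | 1.26 | 1.12 | 8.0% |
| 3 | 0.01 | 1.21 | 1.10 | 7.4% |
| 3 | 0.025 | 1.51 | 1.23 | 11.1% |
| 4 | 0.01 | 1.31 | 1.14 | 8.7% |
| 4 | 0.025 | 1.77 | 1.33 | 14.1% |

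A simulation of 20,000 two-arm trials per setting, with 44 or 45 clinics per arm and a clinic-level analysis, gave close results. For agency ICC 0.025 the type I error was 8.0% (k = 2), 11.4% (k = 3) and 14.6% (k = 4). With agency ICC zero it was 4.8% to 5.2%.

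**Mixture with single-site agencies.** If a share s of clinics is in three-clinic agencies and the rest are single-site, the average VIF is 1 + s × 2 × rho.

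| s | Agency ICC | VIF | Actual type I error |
|---|---|---|---|
| 0.25 | 0.01 | 1.05 | 5.6% |
| 0.25 | 0.025 | 1.13 | 6.5% |
| 0.50 | 0.01 | 1.10 | 6.2% |
| 0.50 | 0.025 | 1.26 | 8.0% |

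**Aim 4.** Readiness and leadership support are measured on directors and providers, so the averaging over 20 dyads used above does not apply. The within-agency correlation of the clinic values then enters VIF directly. Purely as illustration, a correlation of 0.2 to 0.5 with every clinic in a three-clinic agency gives VIF 1 + 2 × 0.2 = 1.4 to 1 + 2 × 0.5 = 2.0, and a type I error of about 10% to 17%. Nothing in the article says where in this range, or outside it, the true value lies.

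**The case against.** The strongest reply has four parts.

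1. **The harm is conditional.** It needs a positive agency correlation that survives adjustment for baseline outcomes and family mediators, and the article gives none. This stands. The mismatch is certain, but its effect on the standard errors is not.

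2. **The larger figures describe an extreme mix.** A reader might infer from the 7-14% rows that the whole trial runs at that level. The article does not support this. Those rows assume that every clinic is in a three- or four-clinic agency, whereas there is a whole list of single-site agencies. Only about 80% of clinics were expected to join, so agencies may also contribute fewer clinics than they have. The mixed scenarios are the fairer guide.

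3. **Reach.** A reader might infer that Aim 3 is affected in the same way. Its hypotheses compare predictors with each other (leadership support with readiness and climate; motivation with other provider variables), not arms. There the issue is only that clinics of one agency are not independent observations. A reader might also infer that Aim 4 is the worst affected. It could be affected more than the child outcomes, but that depends on an unknown correlation. Mega-agencies would add larger clusters if pooled, but the article does not say whether they enter the main comparison, and their choice of condition is a separate problem.

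4. **A condensed article may leave the variance estimator to a fuller document.** This stands only in part. The article names each level and says that clustering is handled at those levels, so it states a rule, and the rule stops below its own unit of randomisation.

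**Conclusion.** The point holds in conditional form. The stated model treats clinics that share one allocation as independent. If clinics of one agency remain positively correlated after baseline adjustment, the standard errors of the Aim 1 and Aim 4 arm contrasts are too small.

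Under the assumed ICCs, the overall error for child outcomes is about 5.6-8% instead of 5% when a quarter to a half of clinics are in three-clinic agencies. It is higher only if multi-site agencies make up more of the sample or are larger. Confidence is high in the structural mismatch. The inflation figures are a range under assumption and not an estimate for this trial. A statement that every arm contrast is certainly anti-conservative would go beyond what the article supports.

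**What to change.** In every model with an arm contrast, keep the three-level structure, use agency-clustered robust standard errors, and base degrees of freedom on the number of agencies. Each single-site agency forms its own cluster, so the added clustering leaves those clinics as separate units. An agency random intercept above clinic is an alternative where there are enough multi-site agencies to support it. It makes the model four-level, and agency and clinic variance can be separated only through the multi-site agencies. State the choice before analysis, and report the number of agencies and the enrolled clinics per agency by arm. For Aim 3, allow for the same non-independence of clinics.

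The cost is small. Agency membership is already on the OMH list used for allocation, and neither new data nor a change to the allocation is needed. Confidence intervals will be somewhat wider. If the agency correlation proves to be nil, little is lost.
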